#### Life quality index

4.8.3

Using the assessment scale for the patient's quality of life (SF-36 scale Chinese version) is used.

All life quality assessment scales will be tested at visits 1, 3, 5, 6, and 7.

#### Safety index

4.8.4

Vital signs (T, P, R, BP), blood, urine, and stool routine, liver function (ALT, AST, TBIL, AKP, GGT), renal function (BUN and CR), ECG.

All safety indexes will be tested at visits 1 and 5.

#### Endpoint event incidence

4.8.5

Select an indicator including the endpoint event incidence rate and time required to reach the endpoint event. The endpoint event is defined as the occurrence of gangrene of lower limbs.

Figure 2 shows the technical route of the whole multicenter RCT.

**Figure 2 F2:**
[figure not shown]
The technical route of the whole multicenter RCT.

### Data collection

4.9

#### Clinical examination

4.9.1

Before the start of the trial, a history of diabetes, current medication, other medical history, and treatment history will be recorded. The anthropometric data will be collected at five time points (baseline, w4, w8, w12, w24), will be collected using standardized inspection procedures including: gender, age, height (shoes removed), weight (after morning urine, fasting status), body mass index (BMI), waist circumference (perimeter of the horizontal plane at the midpoint of the axillary midline from the rib arch to the midpoint of the crotch margin), hip circumference (largest possible hip circumference), waist-to-hip ratio (WHR). Measure vital signs including blood pressure, heart rate, breathing, and temperature.

#### Blood samples

4.9.2

Blood samples will be collected after fasting overnight, including blood glucose levels (baseline, w4, w8), postprandial C peptide and glucose levels at 0.5, 1, 2, and 3 h (baseline, w8), along with HbA1c and blood lipid (baseline, w8). The kit is provided by Depp. Blood samples will be sent to the laboratory of Teaching Hospital of Chengdu University TCM for analysis.

#### Urine samples

4.9.3

Urine samples will be collected (baseline, w8) using a urine sample collection container and will be sent to the laboratory of Teaching Hospital of Chengdu University TCM for analysis.

#### Stool samples

4.9.4

Stool samples will be collected (baseline, w8) using a stool sample collection container and will be sent to the laboratory of Teaching Hospital of Chengdu University TCM for analysis.

#### Adverse events

4.9.5

Adverse events in this study do not include diabetes-related complications including acidosis, water-electrolyte imbalance, and fever recorded in the medical records. The severity of all AEs should be judged, and the determination result should be recorded in the CRF, and the process associated with the AEs should be recorded. The severity of AEs is determined as follows:

Mild AEs: Patients have conscious symptoms and mild reactions, which are tolerable and do not affect normal activities. Symptoms are transient and resolve independently between cycles of medications or during treatment;Moderate AEs: Affects the patient's normal daily activities, the symptoms last for a long time, and may interfere with treatment, and may require immediate intervention by either changing the dose or reducing the number of medications;Severe AEs: Patients with impaired body functions, loss of normal work and living ability, symptoms lasting longer, indicating the need to discontinue the treatment

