## Abstract

**Background::**

Clinical and basic research supports that blood glucose fluctuation is an important predictor of diabetic vascular disease and an etiology of lower extremity atherosclerosis, which is an important pathological basis for lower extremity vascular diseases. Previous Chinese National Natural Science Foundation trials (No. 81503566) have reported that the traditional Chinese medicine Shenqi compound can reduce blood glucose fluctuation and low-grade inflammation, and protect blood vessels; however, there are no high-quality clinical evidences available to support the same. This multicenter randomized controlled trial aims to obtain more clinical evidence to confirm the efficacy and safety of Shenqi compound in type 2 diabetes with lower extremity atherosclerosis.

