**Methods::**

A multicenter RCT will be implemented in this study for a 32-week study period (8 weeks for intervention and 24 weeks for follow-up). Participants will be recruited from the Teaching Hospital of Chengdu University of TCM, Mianyang Hospital of TCM, and Shuangliu Hospital of TCM. Sixty participants will be randomly divided into a treatment group (basic treatment combined with traditional Chinese medicine Shenqi Compound) or a control group (basic treatment combined with Chinese medicine placebo) with 30 participants in each group. Patients will be selected considering the following inclusion criteria: age between 35 and 65 years, and a positive diagnosis for type 2 diabetes with lower extremity atherosclerosis and TCM syndromes. Primary outcome indicator is an arterial color Doppler ultrasound. Secondary outcome indicators include: blood glucose fluctuation indicators (MBG, SDBG, LAGE), islet β-cell function evaluation indicators (Homa-IR, Homa-islet, SG, SCP), inflammation indicators (NLR, CRP, IL-6), blood lipids, and HbA1c. Safety index includes vital signs (T, P, R, BP), blood, urine, stool routine, liver and renal function, electrocardiogram, and adverse event records. The endpoint event is defined as the presence of gangrene in the lower limbs.

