### Groups

4.4

Participants will be divided into two groups: the treatment and control groups. Their basic treatment can maintain the original plan, which includes a hypoglycemic regimen comprising acarbose + insulin detemir, along with antihypertensive drugs, such as ACEI, ARB, diuretics, calcium antagonists, and β-blockers. Following which lipid-lowering drugs like atorvastatin will be administered.

Control group: Basic treatment + Chinese medicine placebo.

Treatment group: Basic treatment + Shenqi compound. One bag of the test drug three times a day, boiled with water before meals, stirred, covered, and sealed for 3 to 5 min, for a period of 4 weeks. Followed by observation for 8 weeks.

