#### Rejection criteria

4.6.5

1.Those who do not to meet either the inclusion or exclusion criteria after enrollment;2.Those who have not used the medicines according to the regulations, cannot judge the curative effect or provide incomplete information;3.Those who have consumed drugs that are forbidden and may influence the judgment of effection;4.Those who have acute infection during the test

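### The adverse-event definition leaves out diabetes-related complications without limiting this to conditions present at baseline, so new events judged diabetes-related are not counted in either arm

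*Protocol article*

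**What the plan says.** The abstract's Background says the trial is meant "to confirm the efficacy and safety of Shenqi compound in type 2 diabetes with lower extremity atherosclerosis". The abstract's Methods lists the components of the safety index, ending with "liver and renal function, electrocardiogram, and adverse event records". Adverse-event records are therefore part of how safety is to be judged.

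Section 4.9.5 opens with a limit on what counts: "Adverse events in this study do not include diabetes-related complications including acidosis, water-electrolyte imbalance, and fever recorded in the medical records". It then sets out three severity grades. Section 4.9.6 requires a report form for adverse events, and section 4.9.7 lists the criteria for relating an event to treatment. One of those criteria asks whether the participant's own diseases or the combination of drugs could account for the event.

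Section 4.8.4 lists the other safety measures, including "liver function (ALT, AST, TBIL, AKP, GGT), renal function (BUN and CR), ECG", and adds: "All safety indexes will be tested at visits 1 and 5". Section 4.8.5 records one diabetes complication separately: "The endpoint event is defined as the occurrence of gangrene of lower limbs".

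**The concern.** An adverse-event definition normally takes in every untoward occurrence on study and leaves cause to a later, documented step. Here a class of events is removed by presumed cause at the point of definition. Grading, reporting and causality assessment all start from what has been called an adverse event, so an excluded event reaches none of them.

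Two things are at stake. First, the safety comparison cannot speak to a class of events that matters in patients with type 2 diabetes on "a hypoglycemic regimen comprising acarbose + insulin detemir". An excess on Shenqi compound would not appear in the adverse-event table, and neither would a reduction. Second, calling an event diabetes-related is a judgement. If the person making it knows the arm, the events left out may differ between arms. Events that never reach a form may not be recoverable at the analysis.

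**Working it through.** No figure in the protocol depends on this definition, so there is nothing to reproduce. The check sets the sections side by side.

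1. **Is the exclusion conditional?** Section 4.9.5 attaches no condition on onset, worsening or severity, and refers to no causality criteria. The only qualifier concerns entry in the medical records, and the text does not say whether this means before or during the trial.

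2. **Could it be meant only for conditions present at entry?** Section 4.9.1 has medical history recorded before the trial starts, so this reading is possible. It is not what is written. Section 4.6.4 also excludes patients with ketoacidosis or another acute metabolic disorder, or with severe infection, in the month before entry. An acidosis seen during the trial would therefore usually be a new episode.

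3. **Is a prior exclusion needed to deal with attribution?** No. Section 4.9.7 already asks about explanation by the participant's diseases. Section 4.9.5 makes the same judgement earlier, without those criteria and without a record.

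4. **Does another section count the excluded events?** Only in part. Gangrene is counted under 4.8.5. Temperature is among the vital signs in 4.8.4, but the safety index is taken at two visits. Section 4.5.3 has participants note symptom changes daily for monthly review, but nothing turns such a note into an adverse event once 4.9.5 has removed it.

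5. **Is there a knock-on effect?** Section 4.6.6 makes a serious adverse event a reason for exit. If a complication is not an adverse event, the text does not say whether a severe one can be a serious adverse event. Sections 4.6.6 and 4.9.5 must be reconciled.

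6. **Who makes the judgement, and do they know the arm?** Section 4.5.6 says blinding of treating researchers and participants would be difficult, and the Discussion calls the trial open label. Against this, 4.4 gives the control group a placebo and 4.5.3 describes it as similar in packaging, appearance and shape. The protocol is not consistent, but on its own description the judgement may be made knowing the arm.

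**Illustration with assumed rates.** The documents give none. With 30 patients per arm and a proportion p having an excluded event, the expected number is 30p and the chance of at least one is 1 − (1 − p)^30.

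| Assumed p | Expected patients of 30 | Chance of at least one |
|---|---|---|
| 2% | 0.6 | 45% |
| 5% | 1.5 | 79% |
| 10% | 3 | 96% |
| 20% | 6 | 99.9% |

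This shows only that the rule is likely to matter in practice unless such events are rare. It says nothing about a difference between arms.

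**The case against.** The best defence is that the sentence is loosely worded and means complications already on file, as section 4.9.1 would support. On that reading one clarifying clause is enough. This has some force. But the clause is absent, and three centres could apply the sentence differently.

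A second defence is that the rule applies to both arms alike, so it need not favour either. That stands as far as direction goes: if the compound reduced diabetic complications, the rule would hide a benefit. It does not remove the point that no difference in these events can be seen.

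A reader might also infer several stronger things that the documents do not support:

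- **That every acidosis, electrolyte disturbance or fever is excluded.** The three are examples of diabetes-related complications. A fever not attributed to diabetes remains an adverse event.
- **That hypoglycaemia is excluded.** It is not named, and whether it belongs to the excluded class is left open.
- **That the rejection rule removes fever a second time.** Section 4.6.5 lists "Those who have acute infection during the test". It concerns infection, not fever, and does not say that rejected patients leave the safety table. Section 4.6.7 keeps dropouts in the analysis.
- **That the missing electrolytes prove a gap.** A laboratory list in a condensed article is weak evidence.
- **That the safety result is biased towards no harm.** No direction is shown.

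**Conclusion.** The concern holds in this limited form. As written, section 4.9.5 takes new or worsening complications judged diabetes-related out of grading, reporting and causality assessment in both arms. The trial cannot then compare the arms on these events, despite its stated safety aim. An under-count that differs by arm is possible, because the judgement may be made knowing the allocation; its direction and size are unknown.

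The conclusion rests on reading the sentence as it stands, without an unwritten restriction to baseline conditions. It depends on no event rate. The sample size and the efficacy analyses are not affected.

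**What to change.** Delete the exclusion from section 4.9.5. In its place:

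- record as an adverse event every new or worsening untoward event after the first dose, in both arms, whatever its presumed cause;
- enter stable conditions present at baseline as medical history, and count them only if they worsen;
- tabulate diabetes-related events by arm in their own row, so that readers can see them apart from other events;
- leave attribution to the criteria in section 4.9.7.

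This changes what is recorded and reported, not how patients are treated. The cost is one amended paragraph with ethics committee approval under section 4.10.3, a few more adverse-event forms, and a safety table that may look less favourable.

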#### Documentation of adverse events

4.9.6

The AE Report Form must be completed according to the circumstances. Some additional information, including the event time, severity, duration, measure adopted, and the outcome should be noted as well.

#### Relationship between adverse event and study treatments

4.9.7

The researchers will assess the relationship between the AE and treatments being studied using the following criteria: appearance of the suspected adverse reaction after administering the treatment; whether the suspected adverse reaction belongs to the known adverse reactions of the investigated drug; whether the suspected adverse reaction disappears after discontinuation of treatment; whether the same reaction reoccurs again after resuming the investigated drug; and whether the suspected adverse reaction cannot be explained by the participant's diseases or consumption of the combination of drugs.

#### Statistical analysis method

4.9.8

We will use the SPSS20.0 software for statistical analysis of the experimental data. Measurement data will be tested by *t* test, expressing as mean ± standard deviation. Paired design *t* test may also be used for intra-group comparisons. The chi-square test will be used for the enumeration data. Rank-sum test will be used for rank data. The comparison of survival rate and survival time between the two groups will be analyzed by Kaplan–Meier curve.

The analysis data set will be selected from the following:

1.Full analysis set (FAS): Including all subjects who received at least one treatment after randomization and having more than one follow-up record. If the case fails to complete the treatment course, the final observation should be implemented instead. The number of subjects who will undergo evaluation for the efficacy at the end point should be the similar to that at the beginning of the trial.2.Per protocol (PP): In accordance with the treatment protocol, the main variables can be determined, and there is no major violation of the experimental protocol.3.Statistical analysis of the main variables: Analyze the data of the full analysis set and the matching plan set.

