#### Source of participants

4.6.1

The participants will be recruited through the outpatient and inpatient departments of the Teaching Hospital of Chengdu University of TCM, Mianyang Hospital of TCM, and Shuangliu Hospital of TCM. We will also include 40 cases of Teaching Hospital of Chengdu University of TCM, 10 cases of Mianyang Hospital of TCM and 10 cases of Shuangliu Hospital of TCM.

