#### Primary outcomes

4.8.1

1.Arterial color Doppler ultrasound. (Assess arterial intimal thickness, degree of sclerosis, plaque, stenosis)^[16,17]^

Arterial color Doppler ultrasound will be tested at Visits 0 and 8.

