#### Secondary outcomes

4.8.2

1.Measurement of blood glucose levels before three meals, 2 h after three meals, and before sleeping; calculation of average blood glucose levels (MBG), standard deviation of mean blood glucose (SDBG), and maximum blood glucose fluctuation (LAGE).2.β-cell function evaluation index: insulin resistance index (HOMA-IR), area under the glucose curve (SG), and area under the C-peptide curve (SCP). Calculating HOMA-IR, SG, and SCP by:Homa-IR (CP) = 1.5 + G 0 min × CP 0 min/2800; Homa-islet (CP) = 0.27 × CP 0 min/(G 0 min − 3.5);SG = (G 0 min + G 180 min)/2 + G 30 min + G 60 min + G 120 min;SCP = (CP 0 min + CP 180 min)/2 + CP 30 min + CP 60 min + CP 120 min;(G 0 min to G 180 min, CP 0 min to CP 180 min, respectively means blood glucose and C-peptide values at each time point after Steamed bun test).^[18,19]^Blood glucose will be tested at visits 1, 3, and 5. β-cell function evaluation index will be tested at visits 1 and 5.3.Blood lipid: total cholesterol (TC), triglyceride (TG), high density lipoprotein cholesterol (HDL-C), and low density lipoprotein cholesterol (LDL-C);4.Inflammation indicators (NLR, IL-6, and CRP)5.HbA1c

Blood glucose will be tested at visits 1, 3, and 5. β-cell function evaluation index, HbA1c, inflammation indicators and blood lipid will be tested at visits 1 and 5.

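### Continuous outcomes are set for an unadjusted t test, with optional within-arm paired tests, although each has a pre-treatment value; ANCOVA on baseline would gain precision from data already collected

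*Protocol article*

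**What the plan says.** Section 4.9.8 of the protocol article (Statistical analysis method) gives the rule for continuous data: "Measurement data will be tested by *t* test". It adds: "Paired design *t* test may also be used for intra-group comparisons". It names no covariate, and it does not say whether the between-arm t test is run on final values or on change from baseline. Enumeration data go to a chi-square test, rank data to a rank-sum test, and survival comparisons to Kaplan–Meier curves.

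The outcome sections show a pre-treatment value for each continuous outcome:

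- Ultrasound, which includes intimal thickness (4.8.1): "Arterial color Doppler ultrasound will be tested at Visits 0 and 8".
- Glucose indices (4.8.2): "Blood glucose will be tested at visits 1, 3, and 5". Section 4.9.2 gives the matching calendar times, "including blood glucose levels (baseline, w4, w8", so visit 1 is the baseline visit.
- Other laboratory outcomes (4.8.2), with beta-cell indices and HbA1c in the same sentence: "inflammation indicators and blood lipid will be tested at visits 1 and 5".
- SF-36 (4.8.3): visits 1, 3, 5, 6 and 7.

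Section 4.6.1 plans 40 participants at the main hospital, plus "10 cases of Mianyang Hospital of TCM and 10 cases of Shuangliu Hospital of TCM".

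**The concern.** Two separate things are at stake.

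**Precision.** A baseline value that correlates with the follow-up value explains part of the between-patient variation. A t test on final values leaves that variation in the error term. A t test on change uses the baseline, but with a fixed coefficient of 1, which adds noise when the correlation is modest. ANCOVA estimates the coefficient. The trial has 30 per arm and expects losses, and the Discussion lists the limited sample size as a weakness, so unused precision matters.

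**Interpretation.** A paired test within one arm does not compare treatments. Both arms keep their basic treatment (4.4) and receive lifestyle advice (4.5.2), so both can improve without any effect of the compound. The plan permits within-arm p-values and does not rank them below the between-arm comparison. That leaves room to report a significant change in one arm but not the other as if it were a treatment effect.

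**Working it through.** **Inputs from section 4.5.7:** difference δ = 2.0 and SD σ = 2.41, both for SDBG; critical values 1.64 and 1.28; 20% loss. From 4.5.4: 30 per arm. SDBG is a secondary outcome, but it is the only one with planning figures; none are given for the ultrasound primary outcome.

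**Assumption:** the baseline-to-follow-up correlation r is not in the document. The range 0.3 to 0.7 is shown, with equal SD at both times.

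**1. The plan's own figure.** n = 2 × [(1.64 + 1.28) × 2.41 / 2.0]² = 24.76 per arm, hence 25 per arm and 50 in total, as stated. 50 × 1.2 = 60, also as stated. The calculation is for an unadjusted comparison of two means. The value 1.64 is the one-sided 5% point.

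**2. Unadjusted power.** Evaluable per arm: 30 × 0.8 = 24. The standard error is 2.41 × √(2/24) = 0.696, and 2.0 / 0.696 = 2.87. The noncentral t distribution with 46 degrees of freedom gives power of 80.4% at two-sided 0.05. Two less pessimistic cases are 24 per arm at one-sided 0.05, about 88%, and 30 per arm at two-sided 0.05, 88.5%.

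**3. Alternatives at 24 per arm, two-sided 0.05.** The effective SD is σ√(1 − r²) for ANCOVA and σ√(2(1 − r)) for a t test on change.

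| r (assumed) | ANCOVA SD | ANCOVA variance ÷ final-value variance, 1 − r² | 24 per arm works like | ANCOVA power | Change-score SD | Change-score power |
|---|---|---|---|---|---|---|
| 0.3 | 2.299 | 0.91 | 26 | 84% | 2.852 | 66% |
| 0.5 | 2.087 | 0.75 | 32 | 90% | 2.410 | 80% |
| 0.7 | 1.721 | 0.51 | 47 | 98% | 1.867 | 95% |

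The fourth column is 24 / (1 − r²). The ratio of ANCOVA variance to change-score variance is (1 − r²) / [2(1 − r)] = (1 + r)/2, that is 0.65, 0.75 and 0.85. ANCOVA has the smaller variance under either reading of section 4.9.8. Its cost is one degree of freedom (45 instead of 46), which moves power by less than 0.1 percentage point here.

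**4. Within-arm tests, as an illustration.** Assume no treatment difference, a fall of 1.0 mmol/L in both arms, r = 0.5 and 24 per arm. The SD of change is 2.41, so the noncentrality is 1.0 × √24 / 2.41 = 2.03. Each paired t test at two-sided 0.05 is then significant with probability 0.495. The active arm alone is significant in 0.495 × 0.505 = 25% of such trials. For common falls of 0.5 to 1.5 mmol/L and r of 0.3 to 0.7, this pattern occurs in about 3% to 25%. A 5% error rate does not govern a claim based on it.

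**The case against.** The strongest reply is that nothing here is an error. Under randomisation the unadjusted t test is valid, and its error rate already allows for chance baseline imbalance. That stands: the loss is of precision and clarity, not of validity.

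The size of the gain is uncertain. The document gives no correlation, and at r = 0.3 the variance ratio is only 0.91, a gain of about 3 to 4 percentage points of power over final values. That also stands. So does the remark that power of about 80% is the pessimistic end, since it takes the full 20% loss and a two-sided test.

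Several stronger readings are tempting but not supported:

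- **Every outcome has a baseline.** Gangrene has none and goes to Kaplan–Meier curves. Ultrasound findings recorded as grades or categories would fall under the rank-sum or chi-square rule, and linear ANCOVA is not meant for them.
- **Baseline is discarded.** Section 4.9.8 does not say so; a t test on change would use it. ANCOVA is still the more precise of the two.
- **Repeated outcomes are tested visit by visit.** The text does not say this.
- **Efficacy rests on the paired tests.** They are optional and are not declared the basis of any conclusion. The risk is that they are permitted without being ranked.

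Finally, a centre term, a repeated-measures model and transformation of skewed markers are details that an article may leave to the analysis plan, and their absence is no finding. The same defence does not cover the t test itself, because the article names that method.

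**Conclusion.** The point holds as a free improvement for the continuous outcomes: continuous ultrasound measures such as intimal thickness, glucose indices, beta-cell indices, lipids, inflammation markers, HbA1c and SF-36. The article fixes a valid but less efficient between-arm test and permits within-arm tests that answer a different question.

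For SDBG under the protocol's planning values, ANCOVA raises two-sided power with 24 per arm from about 80% to between 84% and 98%, depending on an assumed r of 0.3 to 0.7. The gain is small at the lower end and substantial from about 0.5. These figures rest on equal SDs at baseline and follow-up and on the full 20% loss. They cannot be carried over to the ultrasound primary outcome in numbers, because the article gives no SD or effect for it; the direction of the argument is the same. Nothing in the document suggests that the planned between-arm test is biased.

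**What to change.** In section 4.9.8, for continuous outcomes:

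1. Define the efficacy result as the between-arm difference, with its 95% confidence interval, from an ANCOVA of the follow-up value on arm and baseline value. Centre may be added as a further term, given the planned 40/10/10 split.
2. Report within-arm change as mean and SD only, without p-values, and state that treatment conclusions come from the between-arm difference.

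Keep the existing rules for graded, categorical and time-to-event data. A repeated-measures model for glucose indices and SF-36, and transformation of skewed markers, are optional and can be left to the analysis plan.

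The cost is a few sentences. No visit, assay or participant is added, and every baseline value needed is already scheduled.

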#### Sample size

4.5.7

We aim to select a sample size estimation method when comparing the two sample means. The following calculation formula may be used when the sample number of the test group and the control group is expected to be equal:
 
[figure not shown]

Here, n represents the estimated sample size of each test group, μα and μβ are the μ values corresponding to α and β, where μα represents the μ value of the probability of a type I error, μβ represents the μ value of a type II error, and δ is consistent with the required degree of discrimination, and σ is the standard deviation of the population. In the formula, μα and μβ can be calculated from the degree of freedom table of the *t*-boundary value υ = ∞−. If the test is required to have a probability of making a type I error >5% and a probability of making a type II error >10%, that is 0.05, β = 0.1, t value table indicated that *t*0.05 = 1.64, *t*0.1 = 1.28, refers to the relevant Chinese medicine treatment of type 2 diabetes blood sugar fluctuations, diabetes combined with lower extremity atherosclerosis.^[11,12]^ The standard deviation of indicator of blood glucose fluctuation–blood glucose (SDBG) in the literature will be set as the clinical efficacy observation, with SDBG <2.0 mmol/L being normal, then σ = 2.41, δ = 2.0. Here, the value of n brought into the formula is about 24.76, so the minimum sample size for this test is 50 cases. The estimated lost follow-up rate is 20%, and the final number of cases included is 60.

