#### Exit criteria

4.6.6

1.Poor effection, along with the subject not following through with the complete treatment course;2.Presence of adverse reactions that are difficult to tolerate, resulting in the subject leaving the study;3.Occurrence of serious adverse events (AEs);4.Complications associated with other diseases during the trial deeming the participant unsuitable to continue the test;5.Subjects withdrawing from the trial without an explanation

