#### Suspension criteria

4.6.7

1.Occurrence of serious safety problems during the test;2.Suspension ordered by the administrative department.

Researchers should strive to contact the participants to ascertain the reasons for dropping out from the study, and to acquire other relevant information such as the last time that they had taken the decoction, and to convince them to finish the examinations as far as they possibly can. If the participants experience any AEs during the study, researchers should provide appropriate treatment for them. The expected dropout rate should be <15%. The dropout cases will be included in the statistical analysis.

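### Carry-forward imputes zero change on the primary outcome and every other outcome with one later reading, and the FAS follow-up condition conflicts with the promise to analyse dropouts

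*Protocol article*

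**What the plan says.** The Statistical analysis method section (4.9.8) fixes both the analysis set and the missing-data rule. The FAS takes patients treated at least once after randomisation and "having more than one follow-up record". For those who do not finish treatment, "If the case fails to complete the treatment course, the final observation should be implemented instead". The same paragraph wants the number evaluated at the end to be close to the number at the start. The main variables are analysed in both the FAS and the per-protocol (PP) set.

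Three other sections bear on this:

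- Rejection criteria (4.6.5) list events after enrolment, including "Those who have not used the medicines according to the regulations, cannot judge the curative effect or provide incomplete information", use of forbidden drugs and acute infection. No analysis set is named.
- Exit criteria (4.6.6) include "Poor effection, along with the subject not following through with the complete treatment course", intolerable reactions and serious adverse events.
- The text under Suspension criteria (4.6.7) says: "The dropout cases will be included in the statistical analysis". It also asks researchers to persuade people who leave to complete their examinations, and expects dropout below 15%.

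On timing, Primary outcomes (4.8.1) puts the ultrasound at Visits 0 and 8. Secondary outcomes (4.8.2) puts blood glucose at visits 1, 3 and 5, and β-cell indices, HbA1c, inflammation markers and lipids at visits 1 and 5. The SF-36 is taken at visits 1, 3, 5, 6 and 7 (4.8.3).

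**The concern.** Carry-forward needs an earlier post-baseline value to carry. Where an outcome has only one post-baseline reading, a patient who misses it has nothing but baseline, so the rule amounts to assuming no change. The *t* test then counts that value as a measurement. This affects the primary outcome and four groups of secondary outcomes.

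The case is not far-fetched. Sections 4.8.2 and 4.9.2 together place visits 1, 3 and 5 at baseline, week 4 and week 8, so Visit 8 comes after week 8. A patient can stop treatment early, attend several visits, enter the FAS, and still have no second ultrasound.

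The stakes are dilution of a real effect and, if missingness differs between arms, a difference that treatment did not cause. Some of the listed reasons for leaving are tied to response or tolerability. The Discussion calls the trial open label, and Blinding (4.5.6) says that participants are hard to blind. The FAS follow-up condition adds a second problem: taken with the rest of the text, it does not settle who is analysed.

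**Working it through.** **1. Post-baseline readings per outcome (4.8.1 to 4.8.3).**

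- Ultrasound (primary): 1 (Visit 8).
- β-cell indices, HbA1c, inflammation markers, lipids: 1 each (visit 5).
- SDBG, MBG, LAGE: 2 (visits 3 and 5).
- SF-36: 4 (visits 3, 5, 6 and 7).

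The zero-change problem is complete for the first two lines. It is partial for glucose and the SF-36, where an interim value may exist.

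**2. Equal missingness.** Let Δ be the true difference in mean change and m the fraction of each arm given its baseline value. Assume that those imputed would otherwise have changed like the rest. The expected estimate is (1 − m) × Δ + m × 0 = (1 − m)Δ. With an assumed Δ of 0.80 SD:

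- m = 15%: 0.85 × 0.80 = 0.68 SD.
- m = 20%: 0.80 × 0.80 = 0.64 SD.

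**3. Unequal missingness, no treatment effect.** Let both arms truly change by c. The expected difference, treatment minus control, is (1 − m_T)c − (1 − m_C)c = c(m_C − m_T). All inputs here are assumed:

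- c = 0.8 SD improvement, 10% versus 20%: 0.8 × 0.10 = 0.08 SD in favour of the arm with less imputation.
- c = 0.8 SD improvement, 10% versus 30%: 0.8 × 0.20 = 0.16 SD, same direction.
- c = 0.8 SD worsening: the same sizes, now in favour of the arm with more imputation.

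**4. What dilution means for power.** The protocol gives no ultrasound effect or SD, so the only available scale is the SDBG calculation in Sample size (4.5.7): "then σ = 2.41, δ = 2.0", with critical values 1.64 and 1.28. It reproduces: 2 × [(1.64 + 1.28) × 2.41 / 2.0]² = 24.76 per group. SDBG is not a single-reading outcome, so this is a borrowed scale. With 30 per arm and the SD held at 2.41:

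| m | Expected difference | Power, one-sided 5% | Power, two-sided 5% |
|---|---|---|---|
| 0 | 2.0 | 94.2% | 89.5% |
| 15% | 1.7 | 86.2% | 78.0% |
| 20% | 1.6 | 82.3% | 73.0% |

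If the 20% were simply absent, 24 per arm would remain, with power 89.1% one-sided and 82.0% two-sided, provided the loss is unrelated to outcome. On that assumption, imputing zeros costs more power than not having the data.

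**5. The FAS condition.** There are two readings of a record:

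- A reading of the outcome analysed. The primary outcome has at most one after baseline, so nobody can have more than one.
- Any follow-up visit. Then patients with none or one leave the FAS, although 4.6.7 includes dropouts and 4.9.8 wants similar numbers at start and end. Patients with two or more visits but no Visit 8 ultrasound stay in and, if they stopped treatment early, get baseline carried forward.

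**6. The rejection list.** Section 4.6.5 names no analysis set, and the FAS definition does not refer to it. The PP definition (treatment as planned, main variables determinable, no major violation) resembles the list closely. Removal from the FAS is a possible reading, not a stated rule.

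**The case against.** Several points on the other side stand.

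- **Rejected patients.** A reader might infer that the protocol deletes all rejected patients from the efficacy analysis. It does not say so, and the PP wording suggests the list may already be meant for that set.
- **Reasons for leaving.** A reader might also infer that patients with poor effect or intolerance are rejected. Those are exit criteria, and dropouts are to be analysed. Such patients could fall out only through the follow-up-record condition.
- **Number affected.** It is tempting to apply the 20% in Sample size and say that 12 of 60 patients are imputed. That figure is loss to follow-up, whereas carry-forward is triggered by not completing treatment. Section 4.6.7 expects under 15%, some who stop will still be examined, and a patient outside the FAS cannot also be carried forward.
- **Direction.** Nothing shows that the bias would favour Shenqi compound. With equal missingness the rule only dilutes. The control arm receives a placebo of similar appearance, which sits oddly with the open-label label and could limit differences in loss between arms.
- **Mitigation.** A PP analysis is planned alongside the FAS. It helps little, because it selects on adherence and on having the outcome.
- **Wording and detail.** The follow-up condition may be a slip for at least one record, which would ease the conflict on the primary outcome. A condensed article may also leave imputation detail to a fuller document.

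None of this removes the core: carry-forward and the FAS condition are stated rules, and they do not fit the stated visit schedule.

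**Conclusion.** The point holds in a limited form. For FAS members who stop treatment and lack the single later reading, the stated rule sets change to zero on the primary ultrasound, β-cell indices, HbA1c, inflammation markers and lipids. A true difference is multiplied by 1 − m. At an assumed 15–20% in both arms, an assumed 0.80 SD becomes 0.68–0.64 SD, and the real dilution should be no larger if dropout stays within the protocol's own figures. Unequal imputation adds a false difference of c times the gap in m; its size and direction cannot be worked out from the document.

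Separately, the FAS condition is either impossible to meet on the primary outcome or contrary to the promise to include dropouts. The status of rejected patients is ambiguous, and that ambiguity is not evidence of biased exclusion. Because these rules govern the primary analysis, they should be settled before outcome data are seen.

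**What to change.** 1. Analyse all randomised patients in the arm to which they were assigned, and delete the condition on more than one follow-up record.
2. State that the criteria in 4.6.5 define only the PP set.
3. Replace carry-forward. For single-reading outcomes use multiple imputation with baseline, arm, centre and interim data. For glucose measures and the SF-36 use a likelihood-based repeated-measures model. Add a delta-adjusted sensitivity analysis that shifts the imputed values, by arm, away from the missing-at-random assumption.

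The cost is revised wording and a little more analysis work. No new visits or measurements are needed, and 4.6.7 already asks researchers to obtain final examinations from people who leave.
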